## Abstract

**Introduction:**

Some specific pregnancy disorders are known to be associated with increased incidence of long-term maternal ill health (eg, gestational diabetes with late onset type 2 diabetes; pre-eclampsia with arterial disease). To what degree these later health conditions are a consequence of the woman's constitution prior to pregnancy rather than pregnancy itself triggering changes in a woman's health is unknown. Additionally, there is little prospective evidence for the impact of pre-pregnancy risk factors on the outcome of pregnancy. To understand the importance of pre-pregnancy health requires the recruitment of women into a long-term cohort study before their first successful pregnancy. The aim of this feasibility study is to test recruitment procedures and acceptability of participation to inform the planning of a future large-scale cohort study.

**Methods:**

The prospective cohort feasibility study will recruit nulliparous women aged 18–40 years. Women will be asked to complete a questionnaire to assess the acceptability of our recruitment and data collection procedures. Baseline biophysical, genetic, socioeconomic, behavioural and psychological assessments will be conducted and samples of blood, urine, saliva and DNA will be collected. Recruitment feasibility and retention rates will be assessed. Women who become pregnant will be recalled for pregnancy and postpregnancy assessments.

**Ethics and dissemination:**

The study protocol was approved by South Central Portsmouth REC (Ref: 12/SC/0492). The findings from the study will be disseminated through peer reviewed journals, national and international conference presentations and public events.

**Trial registration number:**

http://www.clinicaltrials.gov; NCT02419898.

Strengths and limitations of this studyWe recognise that there are a number of potential difficulties in the recruitment of women prior to a first successful pregnancy.We have designed this feasibility study to assess the practicalities of recruitment prior to pregnancy, follow-up in pregnancy and the acceptability of the study procedures.The results of the feasibility study will be used to inform the design of a future large cohort study.The feasibility study does not include long-term follow-up of the participants. This however would be an ambition of a future large cohort study.

## Introduction

The impact of maternal health on the development of the fetus and the long-term health of the child is well known.^1^ However, the impact of pregnancy on mothers’ long-term health has commanded less attention. Some specific pregnancy disorders are known to be associated with an increased incidence of long-term maternal ill health. For example, gestational diabetes with late onset type 2 diabetes,^2^ pre-eclampsia with later arterial disease^3^ and antenatal anxiety and depression with later mental health problems.^4^ It is not known to what degree these later health conditions are a consequence of the woman's constitution prior to pregnancy or whether pregnancy itself triggers permanent changes in a woman's health. For example, does a pregnancy complication such as pre-eclampsia (mainly a disease of first pregnancy^5^) simply reveal an underlying constitution susceptible to arterial disease or cause permanent changes that increase the risk of arterial disease? Currently this question has not been specifically addressed, although some studies have attempted indirectly to provide an answer.^6^ Similarly, many questions remain unanswered, for example: do antenatal anxiety and depression reveal a predisposition to mental health problems or do the hormonal and biochemical changes in pregnancy increase vulnerability to these disorders.

Pre-existing dysfunction, such as insulin resistance or hyperlipidaemia, is exacerbated by pregnancy. Hence the concept of pregnancy as a stressor for long-term chronic disease has been proposed.^7^ Problems may also be inter-related, for example insulin resistance and obesity are risk factors for both pre-eclampsia and gestational diabetes and adequate treatment of insulin resistance may reduce the risk of associated pre-eclampsia as well as ameliorate the effects of hyperglycaemia. Yet, the conditions have opposing effects on fetal growth—retarding and promoting respectively.^8^ The association between pre-pregnancy weight and risk of pre-eclampsia is well established and control of pre-pregnancy weight is considered a high priority.^9^ Linkage between population studies and birth registries has enabled the impact of hyperlipidaemia or higher blood pressures on the risk or pre-eclampsia to be estimated^6^
^10^ but without specific knowledge of the changes during pregnancy. Whereas nutritional deficiencies of vitamin C,^11^ vitamin D,^12^ folic acid^13^ and selenium^14^ have all been linked to pre-eclampsia there is little data to show the importance of pre-pregnancy status, where intervention might be expected to have its greatest impact. Pre-eclampsia has been associated with hypothyroidism after pregnancy^15^ but the impact of pre-pregnancy thyroid status is not known. Finally excessive antiangiogenic activity is thought to be a major factor in the development of pre-eclampsia,^16^ but to what extent this reflects a long-term maternal state is completely unknown. These are some examples, related to one complication of pregnancy, but a similar dearth of knowledge applies to gestational diabetes, preterm labour and other important pregnancy problems.

The effects of socioeconomic, behavioural and psychological factors during pregnancy are well documented.^4^
^17–20^ For example, antenatal depression affects approximately 14% of childbearing women^21^ and existing research suggests that enhanced levels of anxiety and depression symptoms during pregnancy contribute independently of other biophysical risk factors to adverse obstetric and birth outcomes.^22^ Lack of social support also constitutes an important risk factor for maternal well-being during pregnancy and has adverse effects on pregnancy outcomes.^19^ Yet the potential impact of environmental and psychological factors before pregnancy is less well understood and under-researched. Understanding the impact of these pre-pregnancy factors on the outcome of pregnancy has the potential to inform preconceptual care, identified as one of the key challenges for maternity services by National Health Service (NHS) England.^23^

The only example of a substantial pre-pregnancy cohort study is the Southampton Women's Survey (SWS).^15^ The SWS focused on fetal growth and nutrition and its impact on later health. One pilot study addressing longitudinal cardiovascular, renal and lipid function from pre-pregnancy to the postnatal period has recently been published.^24^

To distinguish the influence of pre-pregnancy from pregnancy-specific factors requires large cohort studies of women recruited before their first successful pregnancies. It is crucial to understand the effects of pre-pregnancy biophysical, genetic, socioeconomic, behavioural and psychological factors on maternal health so that women at higher risk of pregnancy and postpregnancy conditions can be identified early and supported accordingly.^24^ In addition to the effects of pregnancy on long-term maternal health, a cohort recruited prior to a first successful pregnancy affords the unique opportunity to understand the impact of pre-pregnancy maternal factors on the outcome (for the mother and baby) of the pregnancy itself. The aim of this present cohort study is therefore to characterise the health status of a community sample of young nulliparous women (aged 18–40), to determine the impact of pre-pregnancy factors on the outcome of a first pregnancy and to assess the impact of a first pregnancy, whether normal or complicated, on later maternal health. Pre-pregnancy factors that are potentially modifiable before conception will be specifically sought. The aim of this feasibility study is to test recruitment procedures and acceptability of participation in order to inform the planning of the major cohort study.

## Methods

### Study design and participants

This is a prospective cohort feasibility study. The full cohort study will have three phases (figure 1). This study will address the feasibility of phases 1 and 2 only.
Phase 1 is a detailed characterisation of nulliparous women.Phase 2 is a detailed assessment of events during and immediately after a first viable pregnancy.Phase 3 of the cohort study is follow-up after normal and abnormal pregnancies to determine long-term pregnancy-specific sequelae for selected mothers.

**Figure 1 BMJOPEN2015009282F1:**
[figure not shown]
Flow chart of study recruitment.

Participants will be nulliparous women of reproductive age (18–40 years), who are not pregnant but could have a planned or unplanned pregnancy during the duration of the study. To meet the specific inclusion criteria participants must be: willing and able to provide informed consent; female; aged 18–40 years; not pregnant and; registered in an Oxfordshire GP practice participating in the study or have a home address in the defined geographical area. Women with a previous live birth or still birth after 24 weeks gestation are excluded from participating in the study. Potential participants will be identified from Oxfordshire GP practice lists or via local advertisement. Pre-pregnancy recruitment will take place between April 2013 and March 2016. Recruitment into phase 2 (pregnancy recruitment) will continue until March 2017 allowing 12 months for the final phase 1 recruit to become pregnant. The final postnatal visit will take place no later than March 2018.

### Study visits

Participants will attend one phase 1 baseline appointment. Once a participant has become pregnant she is eligible to enter phase 2 of the study. Pregnancy will be notified either directly or through the GP or community midwife. The vast majority of women who become pregnant in the UK will present initially to their GP, even women with secondary or tertiary care needs. Most women then receive antenatal care via NHS community services. There is very little private obstetric care in the UK. Participants will attend five visits during pregnancy at the following gestations: 7 weeks, 11–13, 18–20, 28 and 34 weeks. Finally participants will attend one postnatal visit 3 months after delivery. During the final visit, participants will be consented for future long-term follow-up (phase 3).

#### Study measures and procedures

The primary measures for the feasibility study are feasibility of recruitment and acceptability of participation. Data on recruitment pre-pregnancy, retention during and postpregnancy and overall attrition will be collected. Participants will be asked to complete a questionnaire to assess the acceptability of the recruitment and data collection procedures.

The following data will be collected: anthropometry (height, weight, body mass index, waist and hip circumferences, ultrasound measurement of abdominal and thigh fat, bioimpedence measurements); cardiovascular assessments (pulse, peripheral and central blood pressure, arterial stiffness, echocardiography, carotid imaging and endothelial function); samples of fasting and non-fasting blood, urine, saliva and DNA; questionnaire (medical, socioeconomic, behavioural and psychological assessments). The timing of study visits, study procedures and samples to be obtained are summarised in table 1. The validated questionnaires used are listed in box 1. Details of the delivery including mode of delivery and complications, gestation at delivery and neonatal outcome will also be obtained from the hospital records. The standardised assessments will be conducted by trained midwives and echocardiographers. Baseline assessments will take place at the central recruitment site or at GP practices; pregnancy and postnatal assessments will all take place at the central recruitment site.
Box 1Validated measures included in the questionnaireSpielberger Trait Anxiety InventoryHospital Anxiety and Depression ScaleEdinburgh Postnatal Depression ScaleEuroQol 5 DimensionsPain QuestionnaireSocial Readjustment Rating ScaleMultidimensional Scale of Perceived Social SupportGeneralized Self-Efficacy scale

**Table 1 BMJOPEN2015009282TB1:** Data collected at each study visit

	Pre-pregnancy			Pregnancy-gestation in weeks			Postnatal
	Visit 1	Visit 2	Visit 3	Visit 4	Visit 5	Visit 6	Visit 7
	baseline	7 week	11–13 weeks	18–20 weeks	28 weeks	34 weeks	3 months
Anthropometry							
Height, weight, BMI	✓						
Weight			✓		✓	✓	✓
Hip/waist ratio	✓	✓	✓				✓
Bioimpedence	✓		✓		✓		✓
Abdominal and thigh fat ultrasound measurement	✓	✓					✓
Cardiovascular							
Pulse and BP (peripheral and central) and arterial stiffness	✓	✓	✓		✓	✓	✓
Echocardiograph, carotid imaging, and endothelial function	✓		✓		✓		✓
Blood							
Fasting	✓		✓		✓		✓
Non-fasting		✓		✓		✓	
DNA	✓ (maternal)			✓ (paternal)			
Saliva	✓	✓	✓	✓	✓		
Urine	✓	✓	✓	✓	✓	✓	✓
Fetal ultrasound		✓	✓	✓	✓		
Questionnaire							
Socioeconomic information	✓	✓			✓		✓
Medical history	✓	✓					
Pregnancy history	✓	✓					
Family history	✓	✓			✓		✓
Tobacco/alcohol/drug use	✓	✓			✓		✓
Diet and exercise	✓	✓			✓		✓
Mental health and well-being study acceptability	✓	✓			✓		✓

BMI, body mass index; BP, blood pressure.

### Outcomes

#### Primary outcome

The recruitment of 300 nulliparous women into phase 1 and the follow-up of 100 women into phase 2 to prove feasibility of the cohort study.

#### Secondary outcomes

##### Recruitment and data collection

The retention of participants in phase 2The incidence of pregnancy within 12 months of recruitmentThe live birth rateThe incidence of pregnancy loss in phase 2 participantsThe incidence of loss to follow-upThe proportion of participants who provide full data at baseline and throughout pregnancy

##### Acceptability

The acceptability of the recruitment strategy to participantsThe acceptability of the data collection procedures to participants

### Sample size

As this is a feasibility study to test recruitment and acceptability, no formal power calculations were undertaken. Eight four per cent of women planning a pregnancy will conceive within 12 months and 25% of nulliparous 20–35 year olds will deliver a child within 3 years.^25^ Data from the SWS (where nulliparous women were recruited regardless of pregnancy intention) showed that almost 25% of pregnancies within 3 months of recruitment were unplanned. Although targeting only women planning pregnancy would yield the highest pregnancy rate, that approach may heavily bias the type of individual recruited. We aim to recruit approximately 150 women planning a pregnancy and a similar number regardless of pregnancy intention. We estimate this will result in 160 pregnancies in the time frame of the study. Given that at least 20% of pregnancies will result in miscarriage^26^ this is likely to result in approximately 130 live births. This number of pregnancies will allow us to adequately test pregnancy recruitment and retention rates, study procedures and their acceptability to recruits.^27^

### Data analysis plan

Analysis of the feasibility study will be descriptive.^28^ The number of participants recruited into phases 1 and 2 during the feasibility study recruitment period will be reported. This will enable us to calculate the staffing requirements, time plan, and the number of centres required to ensure we will recruit to target and on time in the cohort study.

Numbers of pregnancies, live births, adverse events, full data sets and losses to follow-up will be reported as percentages of the total number of participants/pregnancies. This data will enable us to calculate attrition rates for the cohort study. Together with established incidence rates for the outcomes of interest in the cohort study, this will allow us to assess incidence locally and to calculate the number of participants we require at baseline.

Preliminary analysis of the planned cohort study outcomes will be conducted to validate the analysis plan. In addition, the investigators anticipate reporting the longitudinal data obtained from the pilot study.

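### Pregnancy and live-birth percentages of all participants depend on the planned mix of two recruitment groups, so they can size only a main cohort with the same mix

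*Protocol article*

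**What the plan says.** The Sample size section plans two groups: "We aim to recruit approximately 150 women planning a pregnancy and a similar number regardless of pregnancy intention". It expects very different yields from them. For the first, "Eight four per cent of women planning a pregnancy will conceive within 12 months"; for the second, the figure given is that "25% of nulliparous 20–35 year olds will deliver a child within 3 years". Recruiting only women who plan a pregnancy is rejected because "that approach may heavily bias the type of individual recruited". No reason is given for an even split. The two groups together lead to the planning figure: "We estimate this will result in 160 pregnancies in the time frame of the study".

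The Data analysis plan then states that numbers of pregnancies, live births, adverse events, full data sets and losses to follow-up "will be reported as percentages of the total number of participants/pregnancies". It says these data will give attrition rates and, together with established incidence rates, the number of women the main cohort needs at baseline. It mentions no breakdown by recruitment group.

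Two other places bear on the time at risk. Study design and participants sets phase 1 recruitment from April 2013 to March 2016 and keeps phase 2 open until March 2017, "allowing 12 months for the final phase 1 recruit to become pregnant". The secondary outcomes include the incidence of pregnancy in the 12 months after recruitment, again with no split by group.

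**The concern.** A percentage of all participants is a weighted average of two group rates, and the weights come from the recruitment target. It is not a property of either kind of woman. The Introduction describes the main cohort as a sample of young nulliparous women from the community, and nowhere says that it will keep a half-and-half mix. If its mix differs, a baseline number taken from the pooled percentage will be wrong, and on the protocol's own rates it could be wrong by about a factor of two. Sizing the main cohort is one of the stated purposes of this feasibility study.

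A second, narrower concern is follow-up time. The first recruits have about 48 months in which to conceive and enter phase 2, and the last have 12. A crude whole-study percentage averages over these unequal periods.

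**Working it through.** **Inputs** (Sample size section unless noted): 150 women planning a pregnancy, rate 0.84 at 12 months; 150 regardless of intention, rate 0.25 at 3 years; at least 20% of pregnancies miscarry; 12 to 48 months at risk (Study design and participants). The 1,000 births used below are only an illustration.

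**1. Reproduce the plan's figures.** 150 × 0.84 + 150 × 0.25 = 126 + 37.5 = 163.5 pregnancies, against 160 stated. Live births: 160 × 0.8 = 128, or 163.5 × 0.8 = 130.8, against about 130 stated. Both reproduce. If the 25% is instead taken as deliveries, as it is worded, the result is 126 + 37.5/0.8 = 172.9 pregnancies and 126 × 0.8 + 37.5 = 138.3 live births. These fit less well, so the plan appears to have used the 25% as a pregnancy rate.

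**2. Dependence on the mix.** With s the share in the planning group, the pooled pregnancy rate is 0.84s + 0.25(1 − s):

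| s | Pooled pregnancy rate |
|---|---|
| 0 | 25.0% |
| 0.25 | 39.8% |
| 0.50 | 54.5% |
| 0.75 | 69.3% |
| 1 | 84.0% |

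These use the rates as the protocol gives them, a 12-month rate for one group and a 3-year rate for the other.

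**3. Effect on sizing.** Suppose the main cohort is recruited wholly regardless of intention (an assumption) but sized for 1,000 live births on the pooled rate.

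- *25% read as pregnancies throughout:* pooled live-birth rate 0.545 × 0.8 = 0.436, so N = 1,000/0.436 ≈ 2,294. The true rate in that cohort is 0.25 × 0.8 = 0.20, giving 2,294 × 0.20 ≈ 459 births, or 46% of target. The number needed is 5,000.
- *25% read as deliveries throughout:* pooled live-birth rate (0.84 × 0.8 + 0.25)/2 = 0.461, so N = 1,000/0.461 ≈ 2,170. Births reached: 2,170 × 0.25 ≈ 542, or 54% of target. The number needed is 4,000.

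**4. Follow-up time.** Assume a constant hazard in the second group that gives 25% at 36 months. The rate is then 1 − 0.75^(12/36) = 9.1% at 12 months and 1 − 0.75^(48/36) = 31.9% at 48 months. If the 25% are deliveries and conception must come 9 months earlier, 27 replaces 36 and the figures are 12.0% and 40.0%. A crude whole-study percentage mixes rates across that range.

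**5. The 12-month outcome.** A fixed window removes the problem in step 4 but not the one in step 2. The pooled 12-month rate would be (0.84 + 0.091)/2 = 46.6%, or (0.84 + 0.12)/2 = 48%. That is about 5 or 4 times the rate in women recruited regardless of intention.

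**6. Percentages of pregnancies.** If the 20% loss applies equally in both groups, live births per pregnancy are 80% whatever the mix.

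**The case against.** The other side has a good deal to say.

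- *Time horizon.* A reader might infer that the pregnancy rate has no defined time frame at all. The documents do not support that. Pregnancy within 12 months of recruitment is a listed secondary outcome, and keeping phase 2 open for 12 months after the last phase 1 recruit makes the window observable in principle for every woman. The follow-up point stands only for the all-study pregnancy count and for live births per participant.
- *Denominator.* The plan names both participants and pregnancies. Losses and live births per pregnancy depend little on the mix. This stands, and confines the point to per-participant percentages.
- *Same mix.* If the main cohort keeps the mix, the pooled rate is the right one. A cohort drawn from the community does not exclude women planning a pregnancy, so the 46% to 54% is a scenario and not a forecast.
- *Silence.* The article condenses a fuller protocol, and nothing in it forbids reporting by group. But it does name the denominator and ties these data to the baseline number, so it is fair to ask that it name the split.
- *Importance.* The primary outcome, "The recruitment of 300 nulliparous women into phase 1 and the follow-up of 100 women into phase 2", is a pair of counts that this does not touch, and the analysis is descriptive. This stands and limits the severity.

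**Conclusion.** The point holds in a limited form. As written, the per-participant pregnancy and live-birth percentages depend on the recruitment mix, no split is stated, and the data feed the main cohort's baseline number. On the protocol's own rates the pooled pregnancy percentage is 54.5% at an even split and anything from 25% to 84% otherwise. Under the assumption of a main cohort recruited wholly regardless of intention, sizing on the pooled rate would yield about 46% to 54% of target births. This also takes the 84% and 25% as applying to this study's women, although the 25% refers to ages 20–35 and the study recruits ages 18–40.

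Three stronger readings are tempting and go too far.

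- That the study cannot size the main cohort: group rates could be tabulated and reweighted, since intention must be known to recruit 150 planners.
- That the mixing is arbitrary: the protocol justifies mixing, and only the even ratio is unexplained.
- That 57% of births would be reached (0.25/0.436): this treats the 25% as pregnancies in the pooled rate and as deliveries in the comparison.

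It is a worthwhile and cheap improvement to make before analysis. It is not a flaw in the feasibility study's primary outcome.

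**What to change.** Amend the Data analysis plan as follows.

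- Report pregnancy, phase 2 entry and live birth per participant separately for the two recruitment groups. Show intention recorded at baseline as well, because the group recruited regardless of intention will include some women who are planning a pregnancy.
- Give these rates at the 12-month horizon already listed, and as cumulative incidence from the baseline visit for longer follow-up, so that unequal time at risk is handled.
- State that the main cohort's baseline number will come from the group rates weighted to that cohort's intended mix, and state the mix.
- Percentages of pregnancies can stay as they are. Splitting by recruitment route is not needed for this point.

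The cost is a change of wording and some extra tables. No visits or participants are added, and intention must already be known to fill the planning group. The downside is precision. With 150 women the 95% half-width is 1.96 × √(p(1 − p)/150), which is 5.9 points at 84%, 6.9 at 25% and 8.0 at 50%, against 5.6 for the pooled 54.5% in 300. That loss is small beside the 59-point gap between the plan's two rates.
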